### Randomization

An online platform of randomization method will be used to prevent risk allocation concealment. The permuted block randomization will be performed using the following platform, i.e., https://www.sealedenvelope.com [22]. The randomization will be based on a block method for a block size of four, with A for the intervention group and B for the control group. This block of four has six different possible arrangements of two As and Bs. The randomization with body mass index (BMI) and gender stratification will be conducted to assign participants to either Group SS: intervention group or Group NN: control group. The flow diagram for recruitment and randomization is shown in Fig. 1.

### Study procedure

All data will be collected during a face-to-face interview, blood sampling, and direct anthropometric measurement with the participants at Hospital Serdang starting from before operation until 2 weeks after discharge.

#### Intervention group, Group SS

Group SS will be receiving tailored, more intensive, and ongoing nutrition support and lifestyle advice as compared to Group NN. They will be supplemented with oral nutrition support (ONS), available in 400g/can, providing 226 kcal/serving and 9.6 g protein/serving. ONS will be prescribed according to the patient’s requirement, from 1 to 4 servings a day*.* ONS consumption should be daily from 7 to 14 days until 6 h before the scheduled surgery. Patients are encouraged to consume ONS in a small portion, frequently and in between meals. They also will receive intensive and detailed nutrition counseling at each visit. Nutrition counseling consists of adequate energy and protein according to requirement, fluid and salt intake, replenishment of micronutrients, and controlling blood glucose levels before surgery. Follow-up phone calls will be done from time to time to monitor their progress.

#### Control group, Group NN

Participants in Group NN which is referred to as the control group will receive the standard care of the clinic without getting supplemented with ONS. Nutritional advice will be based on a guideline specifically focused on the treatment of symptoms such as nausea, vomiting, loss of appetite, and diarrhea, and how to deal with the symptoms through nutritional approaches. The advice will be given by clinicians or nurses in the clinic. Those who are identified as having moderate and severe malnutrition will be referred to a dietitian for nutrition counseling. Participants in this group will also have to follow up through phone calls from time to time to assess and monitor their nutritional status before a scheduled surgery. The researcher will attend to any problems faced by participants in this study.

All participants will receive standard postoperative care from clinical and nurse staff with the commencement of free fluids and reintroduction of the normal diet without interference from the researcher or protocol. ONS will be given after surgery, only to the intervention group (Group SS) starting on the first day of nourishing fluid/diet allowance until the day of hospital discharge according to the prescription given. On the other hand, participants in the Group NN would not be given any ONS at postoperatively (Table 2).

**Table 2 Tab2:** ONS allocation

Group	Preoperation	Postoperation
Group 1 (SS)	Supplements	Supplements
Group 2 (NN)	No supplements	No supplements

All participants will have to follow up either at an outpatient clinic or home visit 4 weeks after hospital discharge. Regular (fortnightly) contact with all participants will be maintained for 4 weeks after discharge to monitor their nutritional status and progress. Control groups will be treated exactly as the intervention group apart from the ONS provided.

Participants also will be monitored for complications throughout the study period. Monitoring will occur by daily observation of the participant, checking their medical and nursing notes, and liaising with the attending surgical team and nursing staff. At the same time, complications will be noted as major or minor by using a validated criterion [23].

After the trial ends, participants are encouraged to contact the research team via telephone or email should any issues or concerns arise. Participants will be informed if their assessment results are outside the acceptable or normal range and will be encouraged to seek medical advice. Participants are encouraged to continue physician’s treatment and follow-up after surgery, and if needed, the researcher will help those who are at nutritional risk to seek advice from a dietitian as a continuation of care, regardless of which group (intervention or control group).

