**Table 1 Tab1:**
[figure not shown]
The schedule of enrolment, interventions, and assessments

*−t*_*1*_*:* Outpatient appointment day

*t*_*1*_*:* First day of hospital admission for planned surgery

*t*_*2*_*:* First day of tolerating solid food in the ward

*t*_*3*_*:* 1 day before discharge from hospital

*t*_*x*_*:* 4 weeks after discharge from hospital

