### Primary outcome measure

#### Length of hospital stay

Length of hospital stay will be recorded starting from postoperative day 1 until the day of the patient’s discharge. The total length of hospital stay will be taken during visit 2, the day of the patient’s discharge.

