### Statistical analysis

#### Sample size calculation

A systemic review study in 2016 showed that early feeding has a significantly shorter length of hospital stay (*p*<0.01) compared to the late timing of feeding with a difference of −1.72 days and not associated with an increase in clinically relevant complications [26]. Several other studies also support early nutrition for surgery patients significantly shortening the length of hospital stay [27–29].

LOS was chosen to calculate the sample size because it has been used widely as a primary outcome in most nutrition-related RCT studies [30–32] among patients undergoing surgery. The sample size was calculated based on the data from a study conducted on colorectal cancer patients undergoing surgery [30]. The primary outcome was calculated based on the difference in LOS between two groups (control and intervention group) which was 3.45 days.

A large effect size of 0.8 for clinical significance was assumed, and practicality for this research was considered, with a power (*β*) of 90% and a probability (*α*) of 0.05. Allowing for a “drop-out” rate of 20% for the RCT study, we aim to recruit participants who will be included in each group, with the final sample size calculated as 68 participants with 34 participants in each group, respectively.

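### Both late assessments are timed from discharge, so a shorter stay in the intervention arm means earlier measurement after surgery; this matters mainly for secondary measures at visit 2

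*Protocol article*

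**What the plan says.** **Timing of visits.** The section on the primary outcome fixes visit 2: "The total length of hospital stay will be taken during visit 2, the day of the patient’s discharge". The follow-up paragraph under Control group, Group NN fixes the last visit: "All participants will have to follow up either at an outpatient clinic or home visit 4 weeks after hospital discharge". The last time point in Table 1 agrees: "4 weeks after discharge from hospital".

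Two other statements give different times but also count from discharge. Study procedure describes data collection "starting from before operation until 2 weeks after discharge", and t3 in Table 1 is "1 day before discharge from hospital". The remaining in-ward time point, t2, is "First day of tolerating solid food in the ward". That is not tied to discharge, but it is not a fixed postoperative day either.

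**Primary outcome.** "Length of hospital stay will be recorded starting from postoperative day 1 until the day of the patient’s discharge". For the design difference, Sample size calculation states: "The primary outcome was calculated based on the difference in LOS between two groups (control and intervention group) which was 3.45 days". The same section cites a review with a difference of 1.72 days.

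**What is measured when.** Table 3 places PG-SGA, weight, mid-arm circumference, skinfold and dietary records at visits 2 and 3, handgrip at every visit, and biochemistry at baseline and visit 3 only. The text of Data collection procedure agrees on handgrip and biochemistry, but puts PG-SGA, anthropometry and dietary records at visits 1 and 3.

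**Analysis.** Analysis of results compares the groups on the outcome parameters with a repeated-measures general linear model, in which visit is the time factor.

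**The concern.** The event that starts the clock for visits 2 and 3 is the event the intervention is meant to bring forward. If the intervention works as planned, visit 2 and visit 3 fall on different postoperative days in the two arms, while a repeated-measures model treats each visit as one time point.

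Weight, arm circumference, grip strength and symptom scores can all move in the days after an operation. A difference between arms at visit 2 may then contain two parts: the effect of the nutrition therapy, and the effect of having been measured sooner. Postoperative supplements also stop at discharge, so at visit 2 the length of stay sets both the time since surgery and the duration of postoperative supplementation.

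At stake is the interpretation of the secondary nutritional and functional outcomes, not the primary comparison.

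**Working it through.** **1. Inputs from the protocol article.** Difference in stay: 3.45 days (design) and 1.72 days (cited review), both from Sample size calculation. Visit 2: day of discharge. Visit 3: discharge + 28 days, or discharge + 14 days if the Study procedure statement applies. Group size: 34 per arm, and 34 × 0.8 = 27 after the 20% drop-out.

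**2. Assumed input.** The documents give no control-arm stay, so L = 7, 10 and 14 days are used as a range.

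**3. The plan's own sample size.** With effect size 0.8 and 90% power, n per arm = 2(z_α + z_β)²/0.8². One-sided at 0.05 this gives 2(1.645 + 1.282)²/0.64 = 26.8, so 27, and 27/0.8 = 33.75, so 34: the stated figure. Two-sided it gives 33, and 33/0.8 = 41.25, so 42. Sidedness is a separate matter. Only the 27 to 34 patients per arm are carried forward here.

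**4. Size of the timing gap.** Time since surgery in NN is L at visit 2 and L + 28 at visit 3. In SS it is lower by the difference in stay D at both visits. The relative gap is D/L at visit 2 and D/(L + 28) at visit 3.

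| D (days) | Assumed L (days) | Visit 2: D/L | Visit 3: D/(L + 28) |
|---|---|---|---|
| 3.45 | 7 | 49.3% | 9.9% |
| 3.45 | 10 | 34.5% | 9.1% |
| 3.45 | 14 | 24.6% | 8.2% |
| 1.72 | 7 | 24.6% | 4.9% |
| 1.72 | 10 | 17.2% | 4.5% |
| 1.72 | 14 | 12.3% | 4.1% |

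If the last assessment is at 2 weeks, 3.45/(L + 14) is 16.4%, 14.4% and 12.3%.

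**5. What such a gap can do.** Suppose a measure changes by b SD per day around the visit in both arms. Timing alone then creates a difference of 3.45 × b. The chance of a two-sided 5% result with no other difference is Φ(δ/√(2/n) − 1.96) + Φ(−δ/√(2/n) − 1.96), where δ = 3.45b. The slopes are assumptions; the documents give none.

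| b (SD/day) | δ (SD) | n = 27 per arm | n = 34 per arm |
|---|---|---|---|
| 0.01 | 0.03 | 5.2% | 5.2% |
| 0.02 | 0.07 | 5.7% | 5.9% |
| 0.05 | 0.17 | 9.7% | 11.0% |
| 0.10 | 0.35 | 24.5% | 29.6% |

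The steeper slopes are more plausible in the first postoperative days (visit 2) than five to six weeks after surgery (visit 3).

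**6. Which measures are exposed.** At visit 2, handgrip is exposed on either reading. PG-SGA, weight, arm circumference and skinfold are exposed if Table 3 is followed, and not if the Data collection procedure text is. Biochemistry is exposed only at visit 3.

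**7. Whether a covariate repairs it.** Stay is counted from postoperative day 1 to discharge, and visit 2 is the day of discharge. Days since surgery at visit 2 is therefore essentially length of stay. Adjusting for it would condition on the primary outcome, which is itself affected by treatment.

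**The case against.** The strongest reply is that timing is a consequence of randomised treatment. A comparison of the arms at discharge, or 4 weeks after it, is therefore a valid randomised comparison, and it suits a pragmatic trial whose objective spans the hospital stay and the period after discharge. This stands. A reader might infer that the secondary effects are confounded with the primary one, but that is too strong. The comparison answers a different question from status at a given time after surgery, and the article does not say which is meant.

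Other tempting readings are not supported:

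- **Blood markers at both visits.** Biochemistry is taken only at baseline and visit 3, so nothing of the kind arises at visit 2.
- **Damage to the stated objective.** The primary objective is length of stay. Nutritional and functional status are additional outcomes in the abstract.
- **A definite spurious gain in weight for SS.** This needs a daily rate of weight loss that the documents do not give, and weight at visit 2, which Table 3 has and the text does not.
- **A known direction.** Earlier measurement could favour SS where a measure is still falling and disfavour it where it is still recovering.

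It is also fair to say that a fixed postoperative day has its own imbalance: patients discharged earlier would have been at home and off supplements for longer. And adjustment for time since surgery could sit in an analysis plan that is not shown. But the visit times are fixed in the protocol. An analysis plan cannot recover measurements at a common postoperative day, and the obvious covariate fails at visit 2 for the reason in step 7.

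**Conclusion.** The point holds as a moderate design weakness for secondary outcomes, concentrated at visit 2. Under the protocol's own design effect, SS is assessed on average 3.45 days earlier after surgery at both late visits. With assumed control stays of 7 to 14 days, that is about 25% to 49% of control time since surgery at visit 2 and about 8% to 10% at visit 3. With the 1.72-day difference it is about 12% to 25% and 4% to 5%.

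At visit 3, and hence for all biochemistry, the bias is probably small. At visit 2 it could be material if measures change by 0.05 SD per day or more, which is an assumption. The direction differs by measure, the gap disappears if stay does not differ, and the analysis of length of stay is untouched.

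**What to change.** 1. Time the final assessment from the date of surgery, at one fixed postoperative day with a window, the same in both arms. Make it the main between-arm comparison of secondary outcomes.
2. Keep the visit 2 measurements, but report them as status at discharge together with days since surgery in each arm, not as a treatment effect at a common time point.
3. Do not rely on adjusting visit 2 results for days since surgery.
4. Reconcile the visit definitions: 2 versus 4 weeks after discharge, day of discharge versus one day before, and visit 1 versus visit 2 for PG-SGA, anthropometry and dietary records.

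**Cost.** The number of patients and the number of visits do not change. Patients discharged earlier will have been home and off supplements for longer at the final assessment, and the date may miss a routine clinic appointment, although home visits are already allowed. Trial status reports recruitment as completed on 31 December 2021. If the schedule can no longer be changed, items 2 to 4 still apply at almost no cost, and the visit 3 results should also be shown with days since surgery by arm.

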**Methods:**

This is a pragmatic randomized control trial study where elective admitted patients will be randomly divided into the intervention (SS) or control (NN) group. All data will be collected during a face-to-face interview, anthropometric measurement, blood sampling (albumin, white blood count, hemoglobin, and c-reactive protein), handgrip strength, and postoperative complications. Group SS will be receiving a tailored lifestyle and intensively supplemented with oral nutrition support as compared to Group NN that will receive standard medical care. The primary outcome *for this study is* the length of stay in the hospital. Additional outcome measures are changes in biochemical profile and nutritional and functional status. The effects of intervention between groups on the outcome parameters will be analyzed by using the SPSS General Linear Model (GLM) for the repeated measure procedure.

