**Complications postoperative**				
Length of stay in hospital			/	

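### The stated way of finding complications mainly covers the admission, so observation time depends on length of stay and recorded counts can favour the arm discharged earlier

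*Protocol article*

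**What the plan says.** The relevant paragraph stands in the Control group, Group NN section but applies to all participants. It sets the period: "Participants also will be monitored for complications throughout the study period". The next sentence sets the method: "Monitoring will occur by daily observation of the participant, checking their medical and nursing notes", together with liaison with the surgical team and nurses. Events are then graded as major or minor.

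The same section describes what happens after discharge: "Regular (fortnightly) contact with all participants will be maintained for 4 weeks after discharge to monitor their nutritional status and progress". It adds a clinic or home visit at 4 weeks. Neither is given the task of finding complications.

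Table 3 has a heading for postoperative complications. The only row under it is "Length of stay in hospital", ticked at visit 2. Nothing is ticked there for visit 3.

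The Abstract (Methods) counts complications among the data to be collected: "handgrip strength, and postoperative complications". They do not appear in the primary or secondary outcome sections.

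Length of stay runs from postoperative day 1 to discharge (Primary outcome measure). The Sample size calculation rests on "the difference in LOS between two groups (control and intervention group) which was 3.45 days"; it also cites a review with a difference of 1.72 days.

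The end of follow-up is given in two ways. Study procedure stops data collection 2 weeks after discharge. The Table 1 legend and the Group NN section go to 4 weeks.

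**The concern.** The promised period and the stated method do not match. Daily observation and nursing notes belong to an admission. A site that follows the text could reasonably stop looking for complications once the patient goes home.

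If the gap were equal in both arms, the result would be under-counting only. Here the length of ward observation is the postoperative stay itself, which the intervention is meant to shorten. A complication starting on day 8 would be recorded in a patient still on the ward and could be missed in one already at home. The counts would then lean towards the arm discharged earlier even if the intervention had no effect on complications. The trial could also not show whether earlier discharge was safe. Complications are a large part of the rationale in the Abstract, Background and Discussion, so readers will look at these counts.

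**Working it through.** **Figures available.** The document gives no complication rate, onset timing or expected control-arm stay, so there is no plan figure to reproduce for complications. From the document come the stay differences of 3.45 and 1.72 days, 34 patients per arm, and follow-up to 2 or 4 weeks after discharge. Every other input below is an assumption.

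**1. Length of observation.** If detection ends at discharge, the window ratio (SS to NN) is (L − d)/L, where L is the control stay and d the difference. Assume L = 7, 10 or 14 days.

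| Window ends at | d = 3.45 | d = 1.72 |
|---|---|---|
| Discharge | 0.51 to 0.75 | 0.75 to 0.88 |
| Discharge + 14 days | 0.84 to 0.88 | 0.92 to 0.94 |
| Discharge + 28 days | 0.90 to 0.92 | 0.95 to 0.96 |

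Example: (7 − 3.45)/7 = 0.51, and (7 − 3.45 + 28)/(7 + 28) = 0.90. Even complete ascertainment to the 4-week visit leaves unequal windows, because that visit is timed from discharge and not from surgery.

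**2. Effect on counts with no true difference.** Assume a 28-day risk of 40% in both arms, exponential onset with time constant τ truncated at day 28, discharge at day 10 (NN) and day 10 − 3.45 = 6.55 (SS), onset independent of discharge, and no detection after discharge. The fraction detected is [1 − exp(−L/τ)]/[1 − exp(−28/τ)].

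| τ (days) | Detected, NN | Detected, SS | Recorded risk, NN | Recorded risk, SS | Gap (points) |
|---|---|---|---|---|---|
| 5 | 0.868 | 0.733 | 34.7% | 29.3% | 5.4 |
| 7 | 0.774 | 0.619 | 31.0% | 24.8% | 6.2 |
| 10 | 0.673 | 0.512 | 26.9% | 20.5% | 6.4 |

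Between 1 − 0.868 = 13% and 1 − 0.512 = 49% of events go unrecorded.

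**3. If some later events are still found.** Suppose a share q of post-discharge events reaches the notes. The gap is then multiplied by (1 − q). With q = 0.5 (assumed), the three gaps become 2.7, 3.1 and 3.2 points.

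**4. A second set of assumptions.** Take a 30-day risk of 30% in both arms, L = 7, 10 or 14 days and τ = 5, 8 or 12 days, again with no detection after discharge.

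| | d = 3.45 | d = 1.72 |
|---|---|---|
| Apparent risk ratio, no true effect | 0.58 to 0.94 | 0.81 to 0.97 |
| Fewer patients recorded in SS, of 34 | 0.6 to 2.5 | 0.2 to 1.1 |

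Across both differences, the approximate chance of a significant result in that direction is 3% to 12%, against a nominal 2.5%.

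**5. Would day 28 from surgery be covered?** A patient discharged on postoperative day k is followed to day k + 28 under the 4-week schedule. With k at least 1, this is day 29 or later, so day 28 is always reached. Under the 2-week statement follow-up ends at day k + 14, which reaches day 28 only if k is 14 or more. Discharge at days 6.55 and 10 would give days 20.55 and 24, both too early.

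**The case against.** Several counter-arguments are sound.

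- A reader might infer that the monitoring works only in hospital. The text does not go that far. Medical notes and the attending surgical team are not limited to the admission and could reveal readmissions or complications treated in clinic. The contacts and the 4-week visit exist in both arms. What stands is that none of these routes is given the task.
- Table 1 and Fig. 2 are not shown and might include complication assessments. Table 3 may have lost a row in extraction, so its missing tick is weak evidence by itself. The mismatch between period and method in the Group NN section does not depend on either table.
- An article leaves operational detail to the full protocol. Here, however, the article states both the period and the method, and they do not fit.
- Complications are not a defined outcome, and no analysis of them is specified. The bias therefore falls on a safety or descriptive table.
- Complications delay discharge, so stay is partly their consequence. The window that matters is the day a patient would have gone home without a complication. If part of the 3.45 days came from preventing complications, the relevant gap would be smaller than 3.45, and so would the bias.

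**Conclusion.** The point holds in a limited form. As written, ascertainment mainly covers the admission. Its length therefore depends on the primary outcome, and recorded complications can be biased in favour of the arm discharged earlier. The direction is the same in every scenario computed with a difference in stay.

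The size is not known. The gap of about 5 to 6 points illustrates one set of assumptions: 40% risk, exponential onset independent of discharge, a 10-day control stay and no detection afterwards. Other choices give a fraction of a patient to about 2.5 patients of 34.

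Two stronger readings are tempting and are not supported. One is that the earlier-discharged arm will show fewer complications. That needs a real difference in stay, and events that start after the earlier discharge and are missed. The other is that the trial's main result is compromised. Length of stay is measured in full in both arms, so this defect leaves the primary comparison untouched. The plan should be corrected because the repair is cheap and readers will use the complication counts to judge whether shorter stay was safe.

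**What to change.** 1. Reconcile the end of follow-up: 2 weeks after discharge in Study procedure against 4 weeks in the Table 1 legend and the Group NN section. The rest depends on this, since day 28 is reached for every patient only under the 4-week schedule.
2. Count complications over one window that starts at surgery and is identical in both arms, for example to postoperative day 28. Extending the count to discharge plus 28 days would not be enough, because that window also moves with discharge.
3. Add a short set of questions on complications and readmissions to the existing fortnightly contacts and to visit 3, with a check of the notes. The Trial status section says recruitment was completed on 31 December 2021; where follow-up has already ended, use a notes review to the same day.
4. Add a complications row to Table 3, ticked for visits 2 and 3.
5. Report complications by arm over the fixed window, and in-hospital counts only as descriptive. Whether to make complications a named secondary outcome is the sponsor's choice and is not needed for this repair.

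The cost is protocol wording and about one extra page on the case report form, with no added patients and, under the 4-week schedule, no added visits. The small downside is that some post-discharge events will be patient-reported and must be checked against the notes.
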